**Aims:**

The primary aim is to investigate the potential benefits of combining anodal tDCS (A-tDCS) with exergame-based training in the rehabilitation of CI in PwMS. The secondary aim is to assess whether the proposed protocol can provide sustained benefits over time.

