**Discussion:**

We hypothesize cognitive improvements in both groups due to exergame training. However, we expect greater improvements in the EG compared with the CG. Furthermore, we hypothesize that the beneficial effects in the EG will be sustained over time.

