### Methodology

Participants will be randomized into two groups: 40 in the experimental group (EG) and 40 in the control group (CG), matched for demographic characteristics (sex, age), EDSS score, and disease duration. All participants will undergo cognitive training using the Neurotablet system, a virtual-reality–based platform incorporating exergames for motor and cognitive rehabilitation. The system includes exercises with adjustable difficulty levels, enabling tailored treatment plans based on individual disability. The rehabilitation program will consist of 10 sessions (1 hour each), delivered 5 days per week for 2 consecutive weeks.

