### Timeline

Outcome measures will be administered at baseline, after the 10 treatment sessions, and at 1-month and 6-month follow-ups. The study duration is estimated at 2 years (Fig 1).

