### Statistical analysis and sample size

Descriptive characteristics of the included patients will be presented as mean ± standard deviation (SD) or median and interquartile range (IQR) for continuous variables and as absolute frequencies and percentages for categorical variables. Baseline characteristics of the patients will be also shown splitting the patients into the two groups of treatments and comparisons will be performed using Chi-squared test of Fisher’s exact test (for categorical variables) and Mann-Whitney U test or t-test (for continuous variables). Results of the SDMT and PASAT tests will be presented over time as Mean ± SD by showing separately the two groups of treatment. The repeated measures ANOVA will be used to assess the effect of treatment, the effect of time, and the interaction effect between time and treatment on the performance of the SDMT and PASAT tests. The sample size was calculated fixing a power of 0.80 and a significance level of 0.05 and we calculated the sample sizes required for between effect, for within effect and for the between–within interaction effects for both the neuropsychological tests, planning of picking as our final sample size the largest one. To calculate sample sizes, means of measurements over time and covariance matrix for the repeated measures were defined for the SDMT and PASAT tests based on clinical expectations and on previous findings [24]. The largest sample size was the one required for the between effect in the analysis of PASAT test, leading to a sample size of 33 patients in each group to detect the treatment effect of magnitude δ = 0.35. This sample size is even more satisfactory for the SDMT test, where a smaller sample size was required. However, assuming a drop-out rate of 20%, we finally need to enroll in 80 subjects with 40 patients per treatment group. After performing the repeated measures ANOVA, in case of presence of differences, we also plan to compare means using paired t-test, adequately adjusting for multiple testing. In case of missing data over follow-up, a multiple imputation by chained equations approach will be used with 10 imputations. Additionally, we will also perform the same analyses, using complete data to check the robustness of the results. A p value less than 0.05 will be considered significant. All the analyses will be conducted with the Statistical Software Stata version 16.0 (Stata Corporation, College Station, TX, USA). Randomization will be performed using computer-generated random numbers.

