## Discussion

This project is designed to explore the synergistic effect of A-tDCS and VR-based cognitive rehabilitation in PwMS. By combining two non-conventional restorative approaches, we aim not only to improve cognitive function but also to determine whether the benefits can be sustained over time.

Previous studies have identified key brain regions implicated in attention, information processing and executive function, such as the left DLPFC, cingulate cortices, cerebellum, and parietal areas [1,25]. Our results may contribute to refining this knowledge, clarifying the neural mechanisms underlying CI in MS, and possibly pointing to new therapeutic targets.

Beyond mechanistic insights, integrating A-tDCS with exergames training may promote greater patient engagement, enhancing adherence to cognitive rehabilitation programs. Improved compliance is expected to translate into more durable rehabilitative outcomes and a tangible impact on quality of life.

We anticipate that the combined, simultaneous (on-line) use of A-tDCS and exergames will outperform VR alone (with sham stimulation) in both efficacy and persistence of effects. If confirmed, these findings would strengthen the rationale for implementing integrated neurotechnological protocols in MS rehabilitation, providing protocols that can be translated into everyday rehabilitation settings.

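### The only follow-up comparison named after the ANOVA is a paired t-test, which cannot show at which visit EG differs from CG or whether a benefit over sham remains at 6 months

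*Protocol article*

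**What the plan says.** All references are to the protocol article.

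- **Main analysis** (Statistical analysis and sample size): a repeated measures ANOVA with this purpose: "assess the effect of treatment, the effect of time, and the interaction effect between time and treatment on the performance of the SDMT and PASAT".
- **Follow-up step** (same section): "in case of presence of differences, we also plan to compare means using paired t-test, adequately adjusting for multiple testing". No other comparison of means is named after the ANOVA. The independent-samples tests in that section are for baseline characteristics.
- **Visits** (Timeline): "Outcome measures will be administered at baseline, after the 10 treatment sessions, and at 1-month and 6-month follow-ups".
- **Design** (Methodology): two randomised groups of 40. They are described as matched on sex, age, EDSS and disease duration, but no patient-to-patient pairs are defined.
- **Aims and hypotheses:** the Abstract attributes improvement in both groups to the exergames and adds that "we expect greater improvements in the EG compared with the CG". On persistence the Aims say "The secondary aim is to assess whether the proposed protocol can provide sustained benefits over time", and the Abstract's Discussion adds "Furthermore, we hypothesize that the beneficial effects in the EG will be sustained over time". The main Discussion makes persistence a contrast with sham: the combination "will outperform VR alone (with sham stimulation) in both efficacy and persistence of effects".

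**The concern.** A paired t-test needs two measurements on the same unit. EG and CG are independent arms, so here the test can only compare two visits within patients. It cannot say whether EG exceeds CG at any visit.

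The exergames are expected to help both arms, so a significant paired change in EG is predicted even if tDCS adds nothing. EG's change from baseline to 6 months mixes the exergame gain with any tDCS gain, and only the contrast with CG separates them. A non-significant change in EG from post-treatment to 6 months does not show persistence over sham either.

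At stake is the step that should locate the effect in time. That matters most for sustained benefit, the secondary aim, which the main Discussion states relative to sham.

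**Working it through.** **1. The plan's own figure.** The section gives 33 per arm for the between effect on PASAT, with δ = 0.35, power 0.80 and significance level 0.05. If δ is read as an ANOVA effect size f, two equal arms give a standardised difference of 2 × 0.35 = 0.70. The F test with 1 and 64 df and noncentrality 66 × 0.35² = 8.085 then has power 0.7997, so 33 reproduces. The sample size therefore rests on a genuine EG-CG test.

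**2. What the ANOVA terms can show.** Assume all four visits enter the model with equal correlation between visits. The interaction has (2 − 1) × (4 − 1) = 3 df. Compare two EG-CG patterns over baseline, post-treatment, 1 month and 6 months:

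- Lost after treatment (0, D, 0, 0): mean D/4; deviations −D/4, 3D/4, −D/4, −D/4; sum of squares 12D²/16 = 0.75D².
- Fully sustained (0, D, D, D): mean 3D/4; deviations −3D/4, D/4, D/4, D/4; sum of squares 12D²/16 = 0.75D².

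The interaction test has the same noncentrality for both, so it cannot tell a benefit that vanishes from one that lasts. The treatment term sees D/4 and 3D/4 respectively. It is larger for the lasting pattern, but it does not isolate 6 months and is diluted by baseline.

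**3. How often within-arm results mislead, ignoring the ANOVA.** Inputs: 40 per arm, two-sided 0.05 unadjusted, and the same true gain g (in SD) in both arms. The visit correlation ρ is an assumption, because the document gives none. The SD of change is √(2(1 − ρ)), which is 0.775 at ρ = 0.7 and 0.632 at ρ = 0.8. The noncentrality is g√40/SD. The power p of one arm's paired test comes from the noncentral t with 39 df, and P(EG only) = p(1 − p).

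| g | ρ | noncentrality | p | EG only |
|---|---|---|---|---|
| 0.2 | 0.7 | 1.63 | 0.357 | 23% |
| 0.2 | 0.8 | 2.00 | 0.496 | 25% |
| 0.3 | 0.7 | 2.45 | 0.666 | 22% |
| 0.3 | 0.8 | 3.00 | 0.833 | 14% |
| 0.5 | 0.7 | 4.08 | 0.978 | 2.1% |
| 0.5 | 0.8 | 5.00 | 0.998 | 0.2% |

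For comparison, a between-arm t-test on change, simulated with equal gains and 33 per arm, rejects in 4.7% of trials, counting both directions.

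**4. With the ANOVA as gate.** This was simulated with four visits, equal correlation, the same gain at every post-baseline visit in both arms, g = 0.2 to 0.3, ρ = 0.7 to 0.8 and 40 per arm. The rate at which EG alone is significant depends on which term opens the gate:

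- interaction must be significant: about 1 to 2%
- treatment or interaction must be significant: about 2 to 3%
- any term, including time alone: about 14 to 23%, or 11 to 24% with Bonferroni over six paired tests

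Bonferroni is no cure. It lowers p in both arms, and p(1 − p) can rise when p starts above one half.

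**5. Power of the contrast that is missing.** For change from baseline at one visit, with n = 33 per arm and two-sided 0.05 before multiplicity adjustment, power is approximately Φ(Δ / (√(2(1 − ρ)) × √(2/n)) − 1.96). For Δ = 0.70 SD it is 0.81, 0.96 and 0.99 at ρ = 0.5, 0.7 and 0.8. For Δ = 0.35 SD it is 0.30, 0.45 and 0.61.

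**The case against.** The strongest reply is that the plan already contains between-arm tests. The treatment and time-by-treatment terms compare EG with CG, and the between effect set the sample size. The paired tests are an addition after the ANOVA, and comparing visits within patients is a legitimate use of them. All of this stands.

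A reader might infer that the primary aim will be answered only by comparisons that ignore the randomised control. The ANOVA terms contradict that. A reader might also infer that superiority will be declared when EG is significant and CG is not. The document nowhere says so. The 14 to 25% in step 3 is therefore not the plan's false-positive rate. It is what would follow if that reading were adopted with no gate.

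It can also be said that the Abstract's wording on sustained effects in EG is partly met by a within-EG comparison. That is fair for the Abstract, but not for the main Discussion, which claims persistence relative to sham.

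The choice of contrasts after an omnibus test is often left to an analysis plan. Here, however, the protocol names the test, and the named test cannot compare the arms. The matching in Methodology does not rescue it, since it describes group balance and not pairs.

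**Conclusion.** The point holds for the follow-up step and should be fixed; it does not invalidate the main analysis. The ANOVA can show that the arms differ somewhere. It cannot show at which visit, or whether a difference from sham remains at 6 months, and the one follow-up test named cannot do so either.

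The risk of a misleading result depends on a trigger that the plan leaves open. With no tDCS effect, EG alone is significant in about 2 to 3% of trials if the treatment or interaction term must be significant first, close to the nominal 2.5% in one direction. It is about 14 to 23% if a time effect alone suffices. Both ranges assume equal gains of 0.2 to 0.3 SD, visit correlation 0.7 to 0.8, 40 per arm with no dropout, unadjusted paired tests, and that such a pattern would be read as a tDCS benefit. At a common gain of 0.5 SD with the same correlations, the unadjusted rate is about 2% or less even without a gate, because both arms are then nearly always significant.

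**What to change.** In Statistical analysis and sample size, make the follow-up comparisons EG-CG contrasts of change from baseline at post-treatment, 1 month and 6 months. Estimate them from the same repeated-measures model, with 95% confidence intervals and the multiplicity adjustment already promised. State that the conclusion on sustained benefit over sham rests on the 6-month contrast. If a gate is kept, name the ANOVA term that opens it; a time effect alone should not.

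Paired within-arm changes may stay as supplementary description, with a sentence saying that they are not used to infer a tDCS effect. Testing the three visits in a fixed order is an option, not a requirement.

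The cost is wording only: same data, visits, software and sample size. The team should accept that single-visit contrasts have limited power if the true difference is nearer 0.35 SD than 0.70 SD. The change should be made before any unblinded analysis.

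### The sustained-benefit aim has no planned between-group estimate at 6 months: follow-up comparisons depend on an unspecified ANOVA result and use a within-patient test

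*Protocol article*

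**What the plan says.** The Abstract (Aims) and the Introduction both state the secondary aim: "The secondary aim is to assess whether the proposed protocol can provide sustained benefits over time". The Timeline section gives four visits: "Outcome measures will be administered at baseline, after the 10 treatment sessions, and at 1-month and 6-month follow-ups".

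Under Statistical analysis and sample size, two things are unconditional:

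- the description by group: "Results of the SDMT and PASAT tests will be presented over time as Mean ± SD by showing separately the two groups of treatment";
- a repeated measures ANOVA, which tests "the effect of treatment, the effect of time, and the interaction effect between time and treatment on the performance of the SDMT and PASAT tests".

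One further step is conditional on that ANOVA: "in case of presence of differences, we also plan to compare means using paired t-test", with a promised correction for multiplicity. The section does not say which of the three ANOVA effects counts as a difference. It names no between-group contrast at any single visit.

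The Abstract (Discussion) adds an expectation that bears on the condition: "We hypothesize cognitive improvements in both groups due to exergame training".

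**The concern.** Whether benefit lasts is a question about the late visits, above all the one at 6 months. The main Discussion also frames it between groups, since it expects active stimulation with exergames to do better than sham with exergames on persistence as well as on efficacy. The natural answer is a 6-month difference between groups with a confidence interval.

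The plan puts two obstacles before that answer. Any comparison of means waits on an ANOVA result that is not specified, so the reading could be settled after the data are seen. And the comparison named is within patients. If the ANOVA is not significant, the report would hold group means and SDs but no planned difference or interval to separate absence of benefit from imprecision. If a between-group estimate were added only after a significant result, it could be too large on average.

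**Working it through.** **1. The plan's own figure.** Inputs from the sample size section: power 0.80, significance level 0.05, δ = 0.35, 33 per arm. Read δ as Cohen's f for the between-group effect. The noncentrality is 66 × 0.35² = 8.085, and the F test on 1 and 64 degrees of freedom has power 0.7997, so 33 per arm reproduces. For two equal groups, f = 0.35 is a difference of 2 × 0.35 = 0.70 SD. Read as a standardised mean difference, 0.35 would need 129 per arm, which does not match.

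**2. What the ANOVA treatment effect measures.** It averages the group difference over all four visits. Take two patterns, in SD units at baseline / end of treatment / 1 month / 6 months:

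- fading to nothing, 0 / 0.5 / 0.25 / 0: average 0.75 ÷ 4 = 0.1875;
- sustained, 0 / 0.25 / 0.25 / 0.25: average 0.75 ÷ 4 = 0.1875.

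The treatment effect cannot tell these apart, although they give opposite answers to the secondary aim.

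**3. What the interaction measures.** It tests whether the group difference varies over the visits. Under the fading pattern above (33 per arm, correlation 0.7), it is significant in about 72% of simulated trials, with a mean 6-month difference of about 0. Significance is not evidence of sustained benefit.

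**4. What the paired t-test measures.** The mean change from baseline in the experimental group is the common training gain plus any stimulation effect. With an assumed common gain of 0.3 SD and no stimulation effect, both groups change by 0.3 SD. The test can be significant in both and says nothing about stimulation.

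**5. Effect of the condition.** Monte Carlo, 8,000 runs per setting: 2 groups × 4 visits, 33 per arm, SD 1, equal correlations of 0.5 or 0.7, common gain 0.3 SD, tests at 0.05, and a baseline-adjusted 6-month group difference. Correlations, gain and true effects are assumptions; the documents do not give them.

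Reading A: treatment or interaction must be significant (correlation 0.5 / 0.7).

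| True difference, three post-baseline visits | Condition met | Follow-up skipped | Mean 6-month estimate when met | Inflation |
|---|---|---|---|---|
| 0.5 / 0.5 / 0.5 | 0.76 / 0.86 | 24% / 14% | 0.55 / 0.53 | 10% / 6% |
| 0.5 / 0.4 / 0.3 | 0.60 / 0.72 | 40% / 28% | 0.36 / 0.33 | 20% / 10% |
| 0.3 / 0.3 / 0.3 | 0.37 / 0.46 | 63% / 54% | 0.43 / 0.39 | 43% / 30% |

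Skipped is 1 minus met; inflation is the mean divided by the true 6-month value, minus 1 (for example 0.43 ÷ 0.3 − 1 = 43%). Repeat runs differ by a point or two, hence the rounded ranges of 14 to 25% skipped and 6 to 12% inflation at 0.5 SD. At a sustained 0.70 SD the condition is met in 96 to 99% of trials with a mean of 0.70 to 0.71, about 2% inflation at most. Under the 0.5 / 0.25 / 0 pattern it is met in about 56 to 75%, with a mean 6-month estimate of about 0.

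Reading B: any effect suffices, including time. With no treatment effect the condition is met in 73% / 91% of trials. With the true effects above it is met in 98 to 100%, and the 6-month estimate is unbiased.

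Reading C: the interaction alone must be significant (6,000 runs per setting, correlation 0.6 or 0.8, 33 or 40 per arm). A sustained 0.35 SD goes untested in 28 to 67% of trials and is overstated by 0.05 to 0.18 SD when tested.

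Reported without a condition, the 6-month difference is unbiased in every setting.

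**The case against.** **The 6-month result is hidden if the ANOVA is not significant.** A reader might infer this, but the documents do not support it. Means and SDs by group over time are shown unconditionally, and with the arm sizes anyone can compute an unadjusted difference and interval. This stands. The interval would, however, be unplanned and wider than need be. With 33 per arm its half-width is 1.96 × √(2/33) = 0.48 SD. Adjusting for baseline multiplies this by √(1 − ρ²), giving 0.42 SD at ρ = 0.5 and 0.34 SD at ρ = 0.7.

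**The 6-month result appears only when it is large, and is then overstated.** Also tempting and also too strong. The condition is an omnibus test over all visits and can be met because of time or an early visit; under the fading pattern it is met often with a 6-month estimate near zero. Inflation vanishes under Reading B and is trivial at 0.70 SD. Moreover, the inflation figures are for a between-group estimate, which the planned paired t-test would not produce. They show what would happen if such an estimate were added under the same condition, not that a planned output is biased.

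**An omnibus test followed by adjusted comparisons is conventional, and which effect triggers them may be in a fuller document.** Fair on both counts. But the article does state a conditional rule and does name a within-patient test. Neither becomes a between-group answer by adding detail about the trigger.

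**Sustained benefit could mean persistence within the experimental group, for which a paired test is apt.** Possible from the wording of the aim alone. The main Discussion nevertheless makes persistence a comparison with sham, and improvement is expected in both groups.

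**Conclusion.** The point holds in this form: as written, the plan gives the secondary aim no between-group 6-month estimate with an interval, whether or not the ANOVA is significant. The treatment effect and the interaction do not substitute for it. That conclusion needs no simulation.

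The size of the selection problem depends on a reading the document does not fix. If treatment or interaction is required, it is material for true differences of 0.3 to 0.5 SD and negligible at 0.70 SD, the difference implied by reading δ as Cohen's f. If time alone suffices, there is no selection and the condition does no work. These figures rest on the assumed correlations, common gain and 33 completers per arm. The matter is worth correcting before analysis but does not undermine the design or the sample size.

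**What to change.** In Statistical analysis and sample size, remove the condition for between-group contrasts and state that:

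- the experimental-minus-control difference in SDMT and PASAT at end of treatment, 1 month and 6 months will be estimated from the repeated measures model, or adjusted for baseline, with 95% confidence intervals;
- these estimates will be reported whatever the ANOVA shows;
- the 6-month difference answers the secondary aim;
- the multiplicity adjustment already promised applies to the p values.

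Paired comparisons within groups may stay as description. The cost is a sentence or two, with no extra patients, visits or change to the 33 per arm. The small downside is that the omnibus test no longer screens these contrasts, which the multiplicity adjustment covers. The article expects data collection to finish by July 2026 and analysis by September 2026, so the change should be made before unblinded results are seen.

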
### Oversight and monitoring

The IRCCS Ospedale Policlinico San Martino, Genoa, will act as coordinating center, responsible for trial oversight, central randomization, data management, monitoring, and communications with the ethics committee and trial registry. Participants will be recruited at three sites (ASL3 Neurology Department, AISM Liguria Rehabilitation Service, and IRCCS Policlinico San Martino). Each site will have a principal investigator responsible for local conduct. A Steering Committee (PI, site PIs, statistician, data manager) will oversee scientific and operational aspects, including protocol amendments, recruitment, adherence, and data quality. Data will be entered into password-protected eCRFs stored on a secure institutional server, with anonymization, restricted access, and regular back-ups. Given the low-risk nature of the trial, no Data Monitoring Committee is planned; safety will be overseen by the PI and site PIs and reported to the ethics committee.

Participants will be withdrawn in case of intolerable adverse events, clinical worsening requiring treatment changes, participant request, or investigator decision for safety. Stimulation parameters will not be modified during the trial. Adherence will be promoted through flexible scheduling, continuous support, and the engaging use of exergames.

Unblinding is not anticipated but may be authorized by the PI in exceptional safety-related circumstances. In case of discontinuation or deviation, all scheduled outcome data (clinical, neuropsychological, and patient-reported) will continue to be collected and included in intention-to-treat analyses.

All adverse events (AEs), whether solicited or spontaneous, will be documented; minor AEs will be managed immediately, while serious/unexpected AEs will be reported promptly to the PI and ethics committee. Any important protocol modifications will be submitted for ethics approval and updated in the trial registry.

Personal data will be collected only for study purposes, stored securely, and anonymized for analysis/publication. The final dataset will be accessible to the PI and study team only; the sponsor has no restrictions on access. No specific ancillary or post-trial care is planned; clinical needs will be managed as per standard practice. Given the minimal risk profile of tDCS and exergames, no specific compensation beyond national regulations is planned.

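### The complete-data rerun named as the robustness check cannot test the missing-at-random assumption behind the multiple imputation

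*Protocol article*

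**What the plan says.** Under Statistical analysis and sample size, the protocol article states that for missing follow-up data "a multiple imputation by chained equations approach will be used with 10 imputations". It adds that the same analyses will be repeated "using complete data to check the robustness of the results". Both the check and its purpose are therefore written down. No other missing-data sensitivity analysis is named in the article.

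The same section plans for loss: "assuming a drop-out rate of 20%, we finally need to enroll in 80 subjects with 40 patients per treatment group".

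Oversight and monitoring says that participants will be "withdrawn in case of intolerable adverse events, clinical worsening requiring treatment changes", on their own request, or by investigator decision for safety. It also commits to continued collection of all scheduled outcomes after discontinuation or deviation, and to their inclusion in the intention-to-treat analyses. Outcomes are measured at baseline, after the 10 sessions, and at 1 and 6 months (Timeline). The secondary aim is sustained benefit.

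**The concern.** Multiple imputation by chained equations, as normally run, assumes that a missing score can be predicted without bias from what was observed. A robustness check should show how far the conclusion depends on that assumption. A complete-data analysis does not relax it. It generally relies on an assumption at least as strong, so comparing the two shows whether the result is sensitive to imputing at all, not whether drop-out was informative.

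Two of the listed withdrawal reasons, adverse events and clinical worsening, can relate to cognitive outcome and could act differently in the two arms. If patients lost from the experimental arm did worse than their earlier scores predict, both analyses could overstate the benefit at 1 or 6 months, agree with each other, and be reported as robust.

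**Working it through.** **1. The plan's own figure, to fix the scale.** The inputs are "fixing a power of 0.80 and a significance level of 0.05" and "leading to a sample size of 33 patients in each group to detect the treatment effect of magnitude δ = 0.35". Reading 0.35 as Cohen's f (an assumption) gives d = 2 × 0.35 = 0.70 SD on the subject mean. With N = 66, the noncentrality is 66 × 0.35² = 8.085 on 1 and 64 df, and the power is 0.7997. The normal formula gives 2 × (1.960 + 0.842)² / 0.70² = 32.04, rounded up to 33 per group. The figure reproduces, so 0.70 SD is a reasonable working difference. With 20% loss, 40 × 0.8 = 32 per arm remain.

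**2. Size of an undetected bias at one visit.** Let π be the fraction missing in the experimental arm, m the mean predicted for them under missing at random, and m − δ their true mean (δ in SD units).

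- True arm mean: (1 − π) × observed mean + π × (m − δ)
- Imputed arm mean: (1 − π) × observed mean + π × m
- Overstatement: π × δ = 0.20 × δ, if the control arm is unaffected

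This gives 0.06, 0.10, 0.16 and 0.20 SD at δ = 0.3, 0.5, 0.8 and 1.0. A simulation with 40 per arm, 10 imputations and 1,500 trials, with δ = 0.5 and no benefit in those observed, gave a true difference of −0.101, an imputed estimate of −0.001 and a complete-data estimate of −0.002. If only one of the four visits is affected, the bias in the mean over visits is a quarter of this: 0.10 / 4 = 0.025 single-visit SD.

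**3. Does comparing the two analyses reveal the problem?** Large-sample simulation: true 6-month difference 0.70 SD, four visits with equal correlation, 20% missing per arm, imputation within arm. The correlations and mechanisms are assumptions.

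| What drives outcome-related loss | Correlation | Complete data | Imputed |
|---|---|---|---|
| Experimental arm: part of the 6-month score not predicted by earlier visits | 0.5 | 0.905 | 0.904 |
| Same | 0.7 | 0.854 | 0.854 |
| Experimental arm: the 6-month score itself | 0.5 | 0.950 | 0.881 |
| Same | 0.7 | 0.946 | 0.816 |
| Same | 0.85 | 0.944 | 0.762 |
| Experimental arm: an observed visit (missing at random) | 0.5 | 0.826 | 0.701 |
| Both arms alike: the 6-month score itself | 0.5 | 0.702 | 0.702 |

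- Rows 1 and 2: full agreement, both biased. By the formula in step 2 these correspond to δ of about 0.205 / 0.20 = 1.0 and 0.154 / 0.20 = 0.8 SD, so the mechanism is a strong one.
- Rows 3 to 5: both biased, but they differ by 0.07, 0.13 and 0.18 SD.
- Row 6: disagreement although imputation is unbiased.
- Row 7: no bias in the difference.

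Agreement therefore does not clear the imputation, and disagreement does not convict it.

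**4. At trial size** (40 per arm, no true effect, 1,500 replicates, correlations 0.5 and 0.7). Under the mechanism of rows 1 and 2, the two analyses rejected in 11% to 13% of trials and gave the same verdict in 94% to 95%. When data were missing completely at random, they gave the same verdict in 97%. The check barely separates the two situations.

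**5. What a tipping-point analysis would show.** Take an observed difference of 0.70 SD with 20% missing, unit SD, and no allowance for imputation variance. Significance is lost at a shift of (0.70 − t × √(2/n)) / 0.20.

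- n = 32: (0.70 − 1.999 × 0.250) / 0.20 = 1.00 SD
- n = 40: (0.70 − 1.991 × 0.2236) / 0.20 = 1.27 SD

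A smaller observed difference would tip sooner.

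**The case against.** The best defence is that a complete-data run beside multiple imputation is conventional, that the article does not claim it detects informative drop-out, and that a delta-adjusted analysis may sit in an analysis plan that is not shown. Part of this stands. A reader might infer that no other check is planned, but the documents cannot show that, and the absence of such an analysis from a condensed article is not itself a finding. What remains is that the article names this rerun as the means of checking robustness, and a stated method can be judged.

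The commitment to collect outcomes after discontinuation also counts. Stopping treatment for worsening or adverse events does not by itself create a missing score. It weakens the link from withdrawal reasons to missing data without removing it, since the sample size still allows for 20% drop-out.

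Blinded participants and assessors and a sham designed to be indistinguishable make a large between-arm difference in loss less likely. Step 3 confirms that the same mechanism in both arms leaves the difference unbiased. At the planned effect, a fairly large shift is needed to overturn significance.

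Three other stronger readings fail:

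- That the two analyses always agree, or carry the same bias. Rows 3 to 5 contradict this.
- That the complete-data run breaches intention-to-treat. It is an addition to the imputed analysis and does not replace it.
- That the bias is a known share of the planned effect. Dividing a one-visit bias by 0.70 SD mixes scales, because on the Cohen's f reading that figure refers to the subject mean over visits.

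**Conclusion.** The point holds in a limited form. The comparison of imputed and complete-data results does not test missing at random: it can reassure when both are biased and alarm when imputation is sound. Harm to the treatment comparison requires outcome-related loss that differs by arm and is not captured by earlier scores.

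Under that assumption, with 20% missing at a visit, the overstatement is about 0.20 × δ SD at that visit (0.10 SD at δ = 0.5), and less in the mean over visits if only that visit is affected. The article gives no drop-out mechanism, drop-out by visit, SD or correlation, so these figures show what could go unseen and do not predict what will happen. The relevance is greatest for the 1- and 6-month visits, on which the sustained-benefit aim depends. This is a worthwhile, inexpensive improvement, not a flaw that invalidates the planned analysis.

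**What to change.** Keep multiple imputation as the main analysis and describe the complete-data run as a descriptive supplement. Name as the robustness check a delta-adjusted (tipping-point) analysis on the same 10 imputed datasets: lower the imputed experimental-arm scores in fixed steps, for example from 0 to 1.5 SD, repeat the analysis at each step, and report the step at which the conclusion changes. That range covers the 1.0 to 1.27 SD at which a 0.70 SD result would tip in step 5 of the working. If the unseen analysis plan already contains such an analysis, a cross-reference is enough.

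The cost is one or two sentences and a few hours of analysis, with no new patients or data. The downside is that the robustness statement may look less favourable. The steps should be fixed before the data are unblinded. The stated timeline allows this, with data collection to finish by July 2026 and analysis by September 2026.
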